### 2.3. Subject Inclusion and Exclusion

To participate in this study, subjects must be 35 to 75 years of age and must either have a previous history of myocardial infarction or have at least one coronary artery stenosis ≥50% confirmed by coronary angiography. In addition, subjects must currently be hospitalized with either unstable angina or an acute non-ST segment elevation myocardial infarction and have taken statin medicine for at least 1 month. From a TCM perspective, study participants must have the diagnosis of BSS. Finally, subjects must have a serum hsCRP level between 3 mg/L and 15 mg/L.

The criteria for exclusion include infection, fever, trauma, burn injury, or surgery within one month prior to recruitment; a concomitant diagnosis of cancer, sexually transmitted diseases, tuberculosis, or rheumatoid arthritis or other autoimmune diseases; or a history of serious pulmonary, hepatic, renal, neurological, psychiatric, or hematological diseases. In addition, subjects must not have previously undergone or currently be planning to undergo surgical intervention for CHD. Patients with severe heart failure indicated by an ejection fraction <35% will be excluded as will those with a reduced platelet count or a tendency to bleed or hemorrhage. Study participants must not currently be taking antibiotics or using TCM preparations that relieve fever or clear internal heat. Finally, patients who may become noncompliant or may participate in other clinical trials will be excluded.

During the course of the study, a subject may be excluded if (1) it is discovered that a subject was misdiagnosed for either BSS or CHD or was otherwise inappropriately accepted for participation in the trial; (2) if a subject misses a significant number of treatments or is missing significant records of data; (3) if subject's blood samples from the first two phases of the study (see Section 2.9) are contaminated or damaged in any way such that reliable data cannot be obtained; or (4) if for any reason (e.g., onset of a mid-study nosocomial infection), patient's inflammatory marker levels may not accurately reflect atherosclerotic inflammation. 

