### 2.5. Randomization and Blinding

A member of the Good Clinical Practice (GCP) Clinical Center of Xiyuan Hospital who is independent of the study will use SAS 9.2 software to perform a block randomization, generating a sequence of 72 random numbers in 1 : 1 allocation between the two groups. In order to conceal the generation, the outcomes will be conducted by another member of GCP Clinical Center using a central randomization; once a patient meets all the criteria, a random number will then be delivered by telephone to the clinical researchers, unblinding only after data is collected for the first phase of the study (see Section 2.9). The number delivered by telephone will determine whether the subject receives the control or experimental therapy. 

Because the color of the STS solution given to the experimental group is unique and challenging to emulate, blinding will be difficult to achieve at the physician and patient levels. In order to minimize biases as much as possible, all other potential sources of information that may reveal treatment allocation to patients (e.g., contents of case report form, patient's random number) will be judiciously guarded. Additionally, the details of treatment allocation will not be disclosed to any patient until the study has concluded, and all study participants will be discouraged from discussing with one another their involvement in the trial. Finally, the clinical researchers will strictly abide by the study's random design and will interact with the patients in each group with as few differences as possible.

Blinding will be maintained at the level of outcome assessment. The individuals performing laboratory blood analyses, data management, and statistical analyses will be independent of the clinical component of the study and will not be provided with any information that may reveal treatment allocation details. 

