### 2.8. Outcome Parameters

Serum hsCRP level will serve as the primary outcome parameter in this study. The levels of other inflammatory mediators, including IL-6, TNF*α*, VCAM-1, CD40 and soluble CD40 ligand (sCD40L), MCP-1, and MMP-9, as measured by enzyme-linked immunosorbent assay (ELISA), will constitute secondary outcome parameters. Additional secondary parameters will include safety and the extent of improvement in angina and BSS symptoms. 

To assess safety, patients will be asked to report any side effects or changes in feelings that they have noticed since the previous phase of data collection. In addition, the results of routine blood, urine, and stool tests, liver and kidney function tests, coagulation tests, and electrocardiogram tests will also be considered in the evaluation of safety. Finally, the clinical researchers will carefully monitor all patients for the potential onset of adverse events, the most severe of which may include arrhythmias, heart failure, recurrent myocardial infarction, myocardial rupture, cerebral infarction, cerebral hemorrhage, sudden cardiac death, and all-cause death. 

To assess improvement in angina symptoms, a scoring system will be applied based on the frequency, duration, and intensity of angina episodes [15, 16]. Similarly, a scoring system will also be used to evaluate BSS based on changes in signs and symptoms such as angina, a pulse of choppy or knotted nature, ecchymoses, dark purple tongue, lips, and gums, and expanded sublingual veins [17].

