### 2.10. Data Management

The principal investigator of this study will collaborate with the director of the GCP Clinical Center of Xiyuan Hospital to schedule and coordinate this clinical trial. The GCP Clinical Center will be responsible for randomizing subjects into treatment groups, monitoring research progress, managing the data, and performing statistical analyses. All those involved in these aspects of the trial will remain blind to the details of treatment allocation.

All patient data will be recorded by trained clinical researchers using a standardized, preprinted, and paper case report form (CRF). Collection, transportation and preservation of all blood samples will be performed by trained staff using a standardized procedure. The Laboratory of Cardiovascular Diseases at Xiyuan Hospital will analyze all blood samples and report all results to the clinical researchers for documentation. At the conclusion of the study, CRFs will be delivered to the GCP Clinical Center and examined for completeness by an individual unassociated with the data collection process. If complete, the CRF will be closed to further revision in preparation for data entry.

At the GCP Clinical Center, a data manager uninvolved with subsequent statistical analysis for the study will be responsible for overseeing data entry. To ensure the reliability of the recorded data, two individuals under the data manager will each independently input a copy of the CRF data into a special database (EpiData 3.1 software, http://www.epidata.dk/). If any data in the CRF is unclear, the data manager will submit a clarification form to the principal investigator of the study, who will then issue an inquiry for the clinical researchers to resolve as soon as possible. The data manager will confirm the correct data according to the clinical researchers' response.

A third individual under the data manager will proofread the two independently completed database records to ensure that they are identical and accurately represent the data in the CRF. If the database records are not identical, the data in question will be confirmed from the original CRF. Once complete, the database records will be locked to further revision.

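### Section 2.3 allows randomised patients to be excluded on an open-ended judgement about the primary marker, or for undefined non-adherence or missing data, with no blinded decision required; this can bias the hsCRP comparison

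*Protocol article*

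**What the plan says.** Protocol article, section 2.3, last paragraph, opens "During the course of the study, a subject may be excluded if" and gives four reasons. Two carry this point:

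- Reason (2): "if a subject misses a significant number of treatments or is missing significant records of data". No number of doses or records is attached.
- Reason (4): "if for any reason (e.g., onset of a mid-study nosocomial infection), patient's inflammatory marker levels may not accurately reflect atherosclerotic inflammation". Infection is given only as an example, and there is no closed list of events.

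Reason (1) covers misdiagnosis or wrong acceptance into the trial. Reason (3) covers unusable blood samples from the first two phases.

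Other sections bear on how these reasons would work:

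- 2.8: "Serum hsCRP level will serve as the primary outcome parameter in this study".
- 2.5: "The number delivered by telephone will determine whether the subject receives the control or experimental therapy". That number goes to the clinical researchers. The same section admits that "blinding will be difficult to achieve at the physician and patient levels".
- 2.10: "The Laboratory of Cardiovascular Diseases at Xiyuan Hospital will analyze all blood samples and report all results to the clinical researchers for documentation". The case report forms reach the blinded GCP Clinical Center only when the study has ended.
- 2.9 and Table 1: randomisation belongs to Phase I. hsCRP is one of the laboratory tests at each phase, whereas samples for the other inflammatory markers are frozen for measurement at the end.

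**The concern.** Randomisation protects the comparison only while patients stay in it whatever happens afterwards. Section 2.3 reaches patients after allocation, and two of its reasons depend on post-randomisation events that may differ by arm.

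Reason (4) is the more serious. It asks whether a patient's inflammatory markers are believable as a measure of atherosclerotic inflammation, and hsCRP is both one of those markers and the primary outcome. An unexpectedly high follow-up value is the kind of result that prompts a search for another explanation. If the search is keener in one arm, high values leave that arm more often.

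Reason (2) selects on adherence and data completeness, with the threshold left to judgement.

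At stake is whether the hsCRP result compares the groups as randomised or compares selected subsets of them. A secondary issue is whether patients excluded for missed treatment remain in the safety evaluation.

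**Working it through.** **1. The plan's own figure.** Section 2.4 takes 60 subjects and allows for 20% non-completion: 60 × 1.20 = 72, or 36 per arm. This reproduces the stated 72. Non-completion of 20% means 36 × 0.20 = 7.2, about 7 patients per arm. I use 7 only as an upper limit on removals. It is an allowance for non-completion in general, not evidence of selective removal. No effect size, SD or power is stated, so there is no power figure to reproduce.

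**2. Who can know what, and when.**

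| | Knows arm during study | Sees hsCRP during study | Source |
|---|---|---|---|
| Clinical researchers | Yes | Yes, by the reporting line | 2.5, 2.9, 2.10 |
| Laboratory | No | Yes | 2.5, 2.10 |
| Data management and statistics | No | Receives forms only at the end | 2.5, 2.10 |

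Exclusion is placed during the study. At that time the clinical group has the clinical picture, the arm and the results together. Section 2.3 does not say that this group decides.

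**3. Size under assumed removal patterns.** Inputs from the documents: 36 per arm (2.4), two-sided 0.05, t-test or Wilcoxon test (2.11). Assumptions: no true effect, normal outcome (log hsCRP in SD units), removals from the experimental arm only.

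Method: 40,000 simulated trials per pattern. Bias = average of (mean of remaining experimental patients − mean of control). Type I error = number of trials with p < 0.05 ÷ 40,000, by t-test.

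| Removed from one arm | Pattern | Bias (SD) | Type I error |
|---|---|---|---|
| 0 | none | 0.00 | 4.9% |
| 2 | random, upper half | −0.05 | 5.1% |
| 4 | random, upper half | −0.10 | 6.4% |
| 7 | random, upper half | −0.19 | 11.0% |
| 2 | highest values | −0.11 | 8.6% |
| 3 | highest values | −0.16 | 11.8% |
| 4 | highest values | −0.21 | 15.9% |
| 7 | highest values | −0.33 | 31.7% |

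Between the two patterns, 4 removed at random from the top quartile of one arm give about 10%. With the Wilcoxon test, removing the highest values gives about 7% to 8% (2 removed) and about 13% (4 removed). If the 4 highest are removed from each arm, the mean difference is unbiased, but the t-test rejects in 8.3% of null trials because it ignores the trimming.

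**4. On the hsCRP scale.** Spurious geometric-mean ratio = exp(bias × SD of log hsCRP). The documents give no SD. With an assumed 0.8, the 4 highest removed give exp(−0.207 × 0.8) = 0.85, and 4 random from the upper half give exp(−0.10 × 0.8) = 0.92. Over an SD of 0.5 to 1.0 these become 0.90 to 0.81 and 0.95 to 0.90. The type I error does not depend on the SD.

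**The case against.** Several objections have force.

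- *The decision-maker is not stated.* A reader might infer that unblinded staff who have seen hsCRP make the exclusions. The documents do not say so. The text does not rule out a blinded decision, and 2.10 has an independent person check the forms for completeness. The inference is strong because of timing and reporting lines, but it remains an inference. What stands is that nothing requires the decision to be blind.
- *Exclusion from the study need not mean exclusion from analysis.* Analysis sets are commonly left to an SAP, which is not shown, and their absence is not the point here. The point is the rule that is stated: the subject is excluded, and no continued follow-up or use of the data is mentioned. An SAP that kept these patients would still have to be reconciled with 2.3.
- *Safety.* It is tempting to conclude that patients who stop treatment for a side effect vanish from the safety results. No section says adverse-event data are discarded, and 2.8 has the researchers watching all patients for adverse events. Only the possibility stands.
- *The large error rates are worst cases.* True. Deleting the top values of one arm is extreme, and mild selection of 2 to 4 patients stays near 5%. Removals from the control arm would push the other way.
- *Reason (3).* Sample damage has no evident link to arm. It costs precision and does not produce the directional bias.
- *The exclusion is a safeguard.* The Discussion (section 3) offers careful selection before enrolment and monitoring for infection during the trial as protection against confounded markers. Before randomisation that is sound. Afterwards, infection can differ by arm through chance or treatment (the experimental arm has a daily infusion that the control regimen does not require), and removing those patients breaks the comparison.
- *It is a pilot.* The limitations in section 3 are candid about power and expectation bias, but do not mention these exclusions. The plan still tests at 0.05 and expects to confirm safety and efficacy.

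**Conclusion.** The point holds in this form: reasons (2) and (4) of section 2.3 allow post-randomisation exclusion without thresholds, a closed list of events or a blinded decision, and reason (4) turns on the primary outcome. They can bias the hsCRP comparison. It is not shown that they will, or in which direction.

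The size is illustrative. With 2 to 4 of 36 removed from one arm, type I error runs from about 5.1% to 6.4% under mild selection and from about 8.6% to 15.9% when the highest values go. This rests on an assumed normal log hsCRP, no true effect, and assumed one-sided removal. Loss of excluded patients from the safety evaluation is possible because the text is silent on keeping them; it is not a stated rule.

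The plan should be changed, because the rule concerns the primary outcome and the wording is easy to correct.

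**What to change.** Replace the post-randomisation exclusion list in section 2.3, and align any SAP, with the following:

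1. The primary analysis includes all randomised patients in their allocated arm and uses every available hsCRP value, whatever the adherence or later infection.
2. A damaged or contaminated sample makes that value missing; the patient stays.
3. Removal is allowed only for ineligibility shown by pre-randomisation data, judged by someone blind to arm and to all post-baseline results.
4. All treated patients stay in the safety evaluation.
5. Infection and non-adherence go to a sensitivity analysis. The qualifying events and the adherence threshold are listed in advance, and cases are flagged blind to arm and hsCRP before database lock.

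These changes concern follow-up and analysis only, not clinical decisions about treatment.

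The cost is more than wording. hsCRP in the primary analysis will be somewhat noisier because of intercurrent infections, which the sensitivity analysis addresses. Phase II and III visits and blood samples must continue for patients who would otherwise have been excluded. The Trial Status section reports recruitment from November 2012, with 10 volunteers by February 2013, so the change needs an amendment, and any exclusions already made should be revisited under the new wording.

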### 2.4. Sample Size Estimation

Because the data required to perform an *a priori* sample size calculation for this study is not available, we have adopted the sample size of a comparable trial for use in this pilot study. The comparable trial investigated the effects of TCM on unstable angina patients undergoing percutaneous coronary intervention and involved 60 subjects randomized into two treatment groups of 30 each [14]. For our pilot study, we will recruit 72 patients to begin the trial, assuming conservatively that 20% of the participants in each treatment group will ultimately not complete the study.

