Several limitations affect the strength of our study design. Due to the unavailability of data needed to perform an *a priori* calculation, we determined the sample size for this study by adopting the number used in a comparable trial that we previously completed [14]. As a result, it is possible that our current study design may have insufficient power to reveal statistical significance at the level we desire. In addition, because the color of the STS solution makes double-blinding difficult, our study will be subjected to potential expectation biases from both clinical researchers and study participants. We will attempt to minimize these biases by maintaining blinding at the patient level to the fullest extent possible and by having clinical researchers interact with all subjects as similarly as possible. Full blinding will be maintained at the data analysis level. Finally, our project represents a single-center study and our results may not be wholly generalizable due to a possible selection bias. In the future, multicenter double-blinded, randomized controlled trials are necessary in order to faithfully establish the potential of STS-statin integrative therapy in treating CHD.

Nevertheless, the results of this trial are expected to clarify the potential of an East-West integrative therapy involving STS and simvastatin in reducing atherosclerotic inflammation in CHD patients. Our results will additionally confirm the safety and efficacy of this integrative therapy in treating CHD. Finally, the protocol of our study will also provide a methodological foundation upon which future clinical studies of integrative medicine may develop. 

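### Section 2.4: recruiting 72 leaves about 57.6 completers, not 60, at the stated 20% loss; 72 retains 30 per arm only if loss is at most 16.7%

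*Protocol article*

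**What the plan says.** Section 2.4 (Sample Size Estimation) explains that the data for an a priori calculation were not available, and continues: "we have adopted the sample size of a comparable trial for use in this pilot study". That trial "involved 60 subjects randomized into two treatment groups of 30 each". The recruitment figure follows: "we will recruit 72 patients to begin the trial", with the reason "assuming conservatively that 20% of the participants in each treatment group will ultimately not complete the study".

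The Discussion (Section 3) repeats the basis among the limitations: "we determined the sample size for this study by adopting the number used in a comparable trial that we previously completed". Section 2.1 gives the same 72 patients randomised 1:1, and Section 2.5 fixes the list accordingly, "generating a sequence of 72 random numbers in 1 : 1 allocation between the two groups". The article gives no other loss rate and no other target for the number completing.

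**The concern.** Section 2.4 takes a size of 60, expects a fifth of each arm to be lost, and recruits 72. A reader will conclude that 72 less 20% gives back 60, and it does not. The 20% is stated as a share of the participants in each group, so it applies to the 36 enrolled per arm and not to the 30 wanted at the end. To allow for a loss of that kind, the target is divided by (1 − loss). The figure 72 is what results from multiplying the target by (1 + loss).

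What is at stake is whether the trial's only sample size justification agrees with itself. Under its own loss assumption, the trial would be expected to finish slightly below the size it says it adopts.

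**Working it through.** **Inputs**

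- Adopted size: 60 in total, 30 per arm (Section 2.4).
- Non-completion: 20% of the participants in each group (Section 2.4).
- Recruitment: 72, allocated 1:1, so 36 per arm (Sections 2.1, 2.4 and 2.5).

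**Reproducing the stated figure**

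- Multiplying by (1 + loss): 60 × 1.20 = 72 and 30 × 1.20 = 36. This matches exactly.
- Dividing by (1 − loss): 60 / 0.80 = 75 in total. Per arm, 30 / 0.80 = 37.5, so 38 per arm and 76 in total with equal arms. The stated 72 is 3 to 4 patients short of this.

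The article prints no formula, so the multiplication is inferred from the exact match.

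**Forward check: what 72 leaves at 20% loss**

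- In total: 72 × 0.80 = 57.6.
- Per arm: 36 × 0.80 = 28.8, so 28 or 29 whole patients per arm and 56 to 58 in total.
- Shortfall against 30 per arm: 1.2 on average, 1 or 2 in whole patients.

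**Loss that 72 can absorb**

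- (72 − 60) / 72 = 12/72 = 16.7%; per arm, 6/36 = 16.7%.

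**Size of the effect (illustration only)**

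The protocol sets no power and no effect size, so the 80% power criterion and the standardised effects below are assumptions. The calculations also treat every non-completer as missing from the comparison.

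- Detectable difference, two-sample t-test, two-sided 5%, 80% power: 0.736 SD with 30 per arm, 0.749 SD with 29, 0.762 SD with 28.
- Power by normal approximation, two-sided 5%:

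| Assumed difference (SD) | 30 per arm | 28.8 per arm | Fall (percentage points) |
|---|---|---|---|
| 0.5 | 49.1% | 47.5% | 1.6 |
| 0.6 | 64.2% | 62.4% | 1.8 |
| 0.7 | 77.4% | 75.7% | 1.7 |
| 0.8 | 87.3% | 85.9% | 1.4 |

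Across this range the cost is under 2 percentage points of power.

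**The case against.** The strongest reply is that Section 2.4 never names 60 as a number of completers. It reports 60 as the number randomised in the comparable trial and does not say how many of those completed. Comparing randomised with randomised, 72 exceeds 60 and nothing falls short. This stands to the extent that the completer target is an inference and must be labelled as one. It does not remove the point: non-completion is the only reason given for going from 60 to 72, and if 60 is not what should remain, 72 has no derivation at all. Reading the 20% as a share of the 30 wanted would give 36, but the sentence applies the percentage to the participants in each group, and 6 lost of 36 is 16.7%.

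A reader might also infer three stronger criticisms, which the article does not support.

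- *That the allowance is wrongly called conservative.* The adverb describes the assumed loss rate, not the way the number was inflated. Whether 20% is a cautious rate depends on the loss to be expected, which the article does not give.
- *That a power, precision or feasibility claim fails.* No such claim is built on 30 per arm. Section 2.4 says no calculation was possible, and the Discussion concedes that power may be insufficient.
- *That the end-of-treatment hsCRP comparison will have only 28 to 29 per arm.* The study runs to Phase III, 30 days after treatment stops, while hsCRP is also measured at Phase II on day 14 (Section 2.9 and Table 1). A patient lost between the two does not complete the study but has already given the day-14 value. The 28.8 therefore counts completers and is not necessarily the number analysed at day 14.

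**Conclusion.** Section 2.4 is wrong as written, on the reading that 60 (30 per arm) is the number to be retained. At the stated 20% loss, 72 recruits leave 57.6 expected completers, 28.8 per arm; 72 leaves 60 only if loss does not exceed 16.7%. The arithmetic is certain. The completer target is inferred, but it is the only reading that connects 60, 20% and 72.

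The consequence is minor: 1 to 2 patients per arm, in a single-centre pilot whose size was borrowed and not calculated. No stated operating characteristic is broken and no planned analysis changes. The point deserves correction because it is a factual slip in the only planning number the protocol gives, not because it threatens the trial.

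**What to change.** Replace the last sentence of Section 2.4 with wording such as: *72 patients retain 30 per arm if non-completion is at most 16.7%; at 20% non-completion about 28 to 29 per arm complete the study.* It would help to add that 30 per arm is the number intended to complete, if that is what is meant. The cost is one sentence, with no change to recruitment, randomisation or analysis.

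If the sponsor prefers to keep 30 per arm at 20% loss, the target becomes 38 per arm (76 in total). That means four more patients, the same change wherever 72 appears in the article, and an extension of the 72-number randomisation sequence in Section 2.5. Given the small shortfall, this is optional.
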